#### Secondary comparisons

The main secondary comparisons are based on the hypothesis that more intensive cessation support will lead to increased abstinence:The effect of the PIM enhanced by OCI (Subgroup A) versus PIM alone (Subgroup B) among non-responders to the phase 1 PIM treatment.The effect of the RIM enhanced by PIM (Subgroup D) versus RIM alone (Subgroup E) among non-responders to the phase 1 RIM treatment.The effect of PIM (Subgroup B+C) versus RIM (Subgroup E+F) among community-recruited smokers.

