**Fig. 1 Fig1:**
[figure not shown]
Study design overview. Abbreviations: R, randomisation; FU, follow-up; PIM, personalised instant messaging; RIM, regular instant messaging; OCI, optional combined intervention. Phase 1 intervention will be conducted during the first month after enrolment and phase 2 intervention will be conducted during the second and third months after enrolment

In the first phase (i.e. baseline), all eligible smokers receive brief cessation advice plus a referral to smoking cessation services. Participants are randomised with an equal probability to receive personalised instant messaging (PIM group) or regular instant messaging (RIM group). Evidence shows that early abstinence predicts long-term abstinence. In the second phase (i.e. 1-month follow-up), participants are assessed as responders (self-reported quitters) versus non-responders (continuing smokers, even a puff in the last 7 days) for the re-assignment of intervention. Non-responders in the PIM group are randomised to receive continued-PIM or additional optional combined interventions (OCI), in which they can choose their preferred interventions including (1) multi-media messages, (2) nicotine replacement therapy sampling, (3) financial incentive for active referral, (4) phone counselling, and (5) family/peer support group chat based on their preference, or a combination thereof. Non-responders in the RIM group are randomised to receive continued RIM or PIM. Responders in both groups continue to receive the initial intervention. All participants receive the 2-stage interventions for 3 months from baseline with 4 follow-ups at 1, 2, 3, and 6 months from treatment initiation.

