### Randomisations and blinding

Within 3 days after baseline recruitment, participants are computer-randomised by an investigator who is not involved in recruitment. The first randomisation assigns participants into the PIM or RIM group with a random permuted block size of 2, 4, and 6 in 1:1 allocation ratio. At 1 month, a second randomisation is conducted among non-responders (smoke for even a puff in the past 7 days). In the PIM group, non-responders are further randomised to receive OCI or continue PIM with a block size of 4, 8, or 12 to ensure an allocation ratio of 3:1. Non-responders in the RIM group are randomised to receive PIM or continue RIM, with an allocation ratio of 1:3. The different allocation ratio in the second randomisation is designed to maximise the statistical power to compare OCI versus RIM, which is the co-primary comparison of the current trial (refer to 2.7). Smoking cessation counsellors, outcomes assessors, and statistical analysts are blinded to the group allocation.

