### Statistical analysis

Intention-to-treat analysis will be used with missing outcomes considered to have not changed from baseline [42]. We will compare the primary and secondary quitting outcomes of the primary comparison by using regression models with and without adjustment for important predictors of cessation outcomes, including previous quit attempts, intention to quit, and nicotine dependence [43]. Similar analysis will be used for co-primary and secondary comparisons, adjusting for multiplicity.

For sensitivity analysis, we will use multiple imputation by chained equation models to impute missing outcomes. Baseline characteristics predictive of abstinence will be included in the imputation model. Complete case analysis, where participants with missing abstinence outcomes are excluded, will be conducted.

For exploratory analysis, *t*-tests, supplemented by multivariable regression models, will be used to compare the baseline characteristics of responders and non-responders to the initial and subsequent treatments. Subgroup analysis by baseline characteristics on quitting outcomes will be conducted by interaction terms.

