This trial has several strengths. The recruitment is conducted in smoking hotspot that serves community-recruited smokers with less access to smoking cessation services and low intention to quit [24]. Proactive recruitment measures, where we take a “foot-in-the-door” approach to mobilise and motivate smokers in community settings, are adopted to recruit a more representative sample of common smokers. According to the TTM model, being ready to change within 1 month is at the preparation stage where outside support is influential to their change [29]. We adapt the frequency of mHealth support to the readiness to quit for a more personalised behavioural support. For non-responders, modifying treatment may be more effective earlier than later [45]. Our prior mHealth trial showed 87.3% (461/528) of non-responders and 69.8% (44/63) of responders at 1 month remained smoking and abstinence at 6 months, respectively [6]. These results supported the need for additional intervention for participants non-responding at the early stage thus to improve the long-term abstinence. For participants already responding to the initial intervention, the remaining initial treatment would be enough.

There are some potential limitations. Due to the nature of adaptive trials with multiple interventions, our study provides limited insight into the mechanisms and effects of each intervention component. Constrained by funding resources, we are not able to assess the long-term effects (e.g. 12 months post-treatment initiation). The quitting outcome at 3 and 6 months enables comparison with most current mHealth smoking cessation trials [1].

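### The secondary PIM versus RIM comparison (B+C against E+F) keeps all responders but unequal fractions of non-responders, and the stated analysis does not correct for this

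*Protocol article*

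**What the plan says.** The last item under Secondary comparisons in the protocol article is "The effect of PIM (Subgroup B+C) versus RIM (Subgroup E+F) among community-recruited smokers". B and C are the non-responders and responders who have PIM throughout. E and F are the same two groups under RIM throughout.

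Membership is set by the second randomisation. Under Randomisations and blinding, PIM non-responders are split between optional combined interventions (OCI) and continued PIM "with a block size of 4, 8, or 12 to ensure an allocation ratio of 3:1", so one quarter remain in B. For the other arm, "Non-responders in the RIM group are randomised to receive PIM or continue RIM, with an allocation ratio of 1:3", so three quarters remain in E. Responders are not re-randomised (Study design): "Responders in both groups continue to receive the initial intervention".

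Under Statistical analysis, the primary comparison uses regression with and without predictors of cessation, "including previous quit attempts, intention to quit, and nicotine dependence". For the rest, "Similar analysis will be used for co-primary and secondary comparisons, adjusting for multiplicity".

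The Discussion reports from an earlier trial that "87.3% (461/528) of non-responders and 69.8% (44/63) of responders at 1 month remained smoking and abstinence at 6 months".

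**The concern.** Whether a participant is in the compared set depends on smoking status at 1 month, and the dependence differs between arms. The PIM pool drops three quarters of its non-responders and the RIM pool drops one quarter. One-month responders are much more likely to be abstinent at 6 months, so the PIM pool looks better because of the allocation ratios, whatever PIM does.

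The regression carried over was written for A+B+C versus D+E+F, which includes everyone randomised and needs no correction. The named covariates are baseline variables and cannot remove selection on a post-baseline status. Adding 1-month status as a covariate would not rescue the comparison either. It conditions on a consequence of phase 1 treatment and no longer estimates the effect in the population that the comparison names.

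This is the only listed contrast of PIM throughout with RIM throughout. The primary comparison cannot stand in for it, because about 402 of 600 PIM participants are expected to be assigned OCI and about 138 of 600 RIM participants to move to PIM.

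**Working it through.** **1. The plan's own figures reproduce.** Sample size and power calculation gives a 5.0% control rate and a risk ratio of 1.83, so the PIM rate is 0.05 × 1.83 = 9.15%. A two-sided 5% test with 80% power (pooled variance, no continuity correction) needs 599 per arm, and power at 600 is 0.801. The plan's 600 per group stands. Subgroup counts:
- C = 600 × 10.7% = 64; F = 600 × 7.7% = 46.
- A = 536 × 3/4 = 402, so B = 536 − 402 = 134.
- E = 554 × 3/4 = 416, so D = 554 − 416 = 138.

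**2. Responder shares in the compared sets.**
- B+C: 64/(134 + 64) = 64/198 = 32.4% (PIM arm 10.7%, so about 3.0-fold).
- E+F: 46/(416 + 46) = 46/462 = 10.0% (RIM arm 7.7%, so 1.3-fold).

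**3. Crude and correct rates at the plan's response rates.** From the Discussion, 6-month abstinence is 44/63 = 69.8% in responders and 1 − 461/528 = 12.7% in non-responders. Assume that both apply in both arms, with no phase 2 effect.
- Crude B+C: (134 × 0.1269 + 64 × 0.6984)/198 = 31.2%.
- Crude E+F: (416 × 0.1269 + 46 × 0.6984)/462 = 18.4%. Risk ratio (RR) 1.70.
- Correct PIM: 0.107 × 0.698 + 0.893 × 0.127 = 18.8%.
- Correct RIM: 0.077 × 0.698 + 0.923 × 0.127 = 17.1%. RR 1.10.

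**4. Complete null.** Give both arms the same response rate r and the same rates within response groups. The share in B+C is r/(r + (1 − r)/4), and in E+F r/(r + 3(1 − r)/4). The rejection probability is Φ((d − 1.96·se0)/se1) plus the negligible other tail, where d is the difference in crude rates and se0 and se1 are its pooled and unpooled standard errors. At r = 7.7%, d = 0.0858, se0 = 0.0354 and se1 = 0.0373, which gives 0.67.

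| r | Responder share, B+C v E+F | Crude rates | RR | Rejects at unadjusted 5% |
|---|---|---|---|---|
| 7.7% | 25.0% v 10.0% | 27.0% v 18.4% | 1.47 | 67% |
| 9.2% | 28.8% v 11.9% | 29.2% v 19.5% | 1.50 | 76% |
| 10.7% | 32.4% v 13.8% | 31.2% v 20.6% | 1.52 | 83% |

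**5. Validated abstinence, overall rate set at 5%.** The protocol gives no validated rates by response, so a range is needed.
- Both rates shrunk by the same factor: RR 1.47 to 1.52; rejection 24% at r = 7.7%, about 26% at 9.2%, 29% at 10.7%.
- Responders at 30%: RR 1.72 (r = 7.7%) to 1.89 (r = 10.7%); rejection 46% to 64%.
- Responders at 40%: RR 1.97 to 2.18; rejection 68% to 84%.

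**6. Multiplicity.** The method is not named. Assuming Bonferroni over 3 to 5 comparisons, and r of 7.7% to 9.2%, rejection is about 44% to 62% on the Discussion's scale and 10% to 15% on the proportionally scaled validated outcome.

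**7. Weighted analysis.** Weights are the inverse of the assignment probabilities: C and F 1/(1/2) = 2; B 1/(1/2 × 1/4) = 8; E 1/(1/2 × 3/4) = 8/3. Responder shares become 128/(128 + 1072) = 10.7% and 92/(92 + 1109) = 7.7%, which are the arm values. Under the null the weighted RR is 1.00, and simulated rejection is about 5% to 6%.

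**The case against.** The strongest objection is that the protocol nowhere says unweighted. It names no estimator, it is a journal article, and a separate analysis plan could supply weights. That is fair as to wording, and a reader should not infer that the trial has committed itself to an unweighted analysis. But the article does more than leave a gap. It fixes the pooled sets, names the target population, and carries over a regression that is right only when everyone randomised is included. Followed as written, that gives the wrong answer.

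A reader might also infer that the trial will very probably declare PIM superior. The documents do not support that in general. It fits the Discussion's rates at an unadjusted 5%. The primary outcome is validated abstinence, where the proportional-scaling figure is 24% to 29%, and the protocol states a multiplicity adjustment that lowers every rate in the working.

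The inputs are soft as well. The Discussion's rates come from an earlier trial and appear to be self-reported, though the text does not say so. Their denominators give 63/(63 + 528) = 10.7%, the intervention-arm response quoted in the sample size section, so they may describe that arm alone. Applying them to both arms is an assumption.

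Finally, a reader might extend the problem, or the weights, to the primary comparison. A+B+C versus D+E+F keeps everyone randomised. Applying these weights there (with A 8/3 and D 8) would cut the responder share to 128/(128 + 1072 + 1072) = 5.6% in PIM and 92/(92 + 1109 + 1104) = 4.0% in RIM, distorting a sound analysis. A versus E, A versus B and D versus E do not mix responders with non-responders, so this pooling problem does not arise there.

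**Conclusion.** The point holds for this one secondary comparison. The distortion of the responder share (32.4% against 10.7%, and 10.0% against 7.7%) follows from the allocation ratios and the plan's expected counts alone. Its effect on the result depends on how strongly 1-month response predicts 6-month abstinence. With the Discussion's rates in both arms, a true risk ratio of 1 appears as 1.47 to 1.52. For validated abstinence at 5% overall, the false risk ratio is about 1.5 under proportional shrinkage and rises to about 2.2 if 40% of responders are validated abstinent. The error rates depend on those assumptions and on the unnamed multiplicity method. The direction does not: the bias favours PIM in every scenario examined, and no multiplicity adjustment or baseline covariate removes it.

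**What to change.** State in the analysis section that B+C versus E+F is analysed by regression with design-based inverse-probability weights and robust standard errors. The weights are 2 for C and F, 8 for B and 8/3 for E; equivalently 1, 4 and 4/3. State also that the primary comparison A+B+C versus D+E+F is not weighted in this way.

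The change needs no new data and alters no treatment. The cost is precision, mainly because each member of B stands for four non-responders. The effective size of B+C, (sum of weights)²/(sum of squared weights), falls from 198 to (64 + 4 × 134)²/(64 + 16 × 134) = 600²/2208 = 163. That of E+F barely moves, from 462 to about 459. Expect a wider interval for the risk ratio than the unweighted model would report.

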### Statistical analysis

Intention-to-treat analysis will be used with missing outcomes considered to have not changed from baseline [42]. We will compare the primary and secondary quitting outcomes of the primary comparison by using regression models with and without adjustment for important predictors of cessation outcomes, including previous quit attempts, intention to quit, and nicotine dependence [43]. Similar analysis will be used for co-primary and secondary comparisons, adjusting for multiplicity.

For sensitivity analysis, we will use multiple imputation by chained equation models to impute missing outcomes. Baseline characteristics predictive of abstinence will be included in the imputation model. Complete case analysis, where participants with missing abstinence outcomes are excluded, will be conducted.

For exploratory analysis, *t*-tests, supplemented by multivariable regression models, will be used to compare the baseline characteristics of responders and non-responders to the initial and subsequent treatments. Subgroup analysis by baseline characteristics on quitting outcomes will be conducted by interaction terms.

### Data management plan

The paper-based data will be scanned, stored on an external hard-disk, and locked in a cupboard with keys kept by the principal investigator. The Qualtrics will be used for data entry. Only the investigators and research staffs of the project will be permitted to access the raw data and/or study records. Data will be kept for 10 years or longer after the study is completed. Individual participants will not be directly identifiable from the dataset to be used for analysis.

### Post-trial qualitative evaluation

Qualitative evaluations using a subsample of participants receiving different intervention strategies will be conducted upon the completion of the 6-month follow-up. The semi-structured interview aims to explore participants’ experience and adherence of the intervention and obtain study feedback. Final sample size was determined by data saturation, which was until there was no new information arising from new interviews. A purposive sampling strategy was used to select a group of participants with varied sociodemographic characteristics (e.g. sex, age), smoking cessation outcomes, and intervention adherence. We anticipate that up to 20 participants will be included subject to data saturation. Additional written (for face-to-face interviews) or oral (for telephone interviews) informed consents will be obtained and all interviews will be audio-recorded and transcribed verbatim. The transcripts will be organised using a thematic framework based on topics specified in the interview guide and emerging themes identified through a process of familiarisation with the transcripts.

## Discussion

This is the first study using a SMART design conducted among community-recruited smokers to inform the delivery and effect of an adaptive mHealth intervention in quitting. The study design allows for multi-level comparisons of participants non-responding to the initial mHealth behavioural support and will inform the construction of adaptive interventions that balance quitting outcomes with resource consumption. mHealth instant messaging is the main gradient of this trial for both treatment groups. Firstly, we will test the effect of the personalised mHealth interaction as compared with regular messages on quitting. The findings may optimise the community-based cessation support and other behavioural change treatments utilising the low-cost and scalable mHealth strategy. Secondly, by re-allocating high-intensity treatment components to non-responders in initial treatment and as demonstrates need (optional interventions), the subsequent treatment provided personalised support while conserved treatment resources. Conventional tobacco treatments are additionally provided in options to encourage self-determination and autonomous motivation [44]. For responders of the phase 1 intervention, we will sustain the original intervention and adjust the content to prevent relapse. This may reduce treatment costs and burden as more intensive treatments are not necessary. This trial will operationalise and inform the development of personalised, adaptive, sequential mHealth treatment decisions made for smoking cessation in “real world” community settings.

This trial has several strengths. The recruitment is conducted in smoking hotspot that serves community-recruited smokers with less access to smoking cessation services and low intention to quit [24]. Proactive recruitment measures, where we take a “foot-in-the-door” approach to mobilise and motivate smokers in community settings, are adopted to recruit a more representative sample of common smokers. According to the TTM model, being ready to change within 1 month is at the preparation stage where outside support is influential to their change [29]. We adapt the frequency of mHealth support to the readiness to quit for a more personalised behavioural support. For non-responders, modifying treatment may be more effective earlier than later [45]. Our prior mHealth trial showed 87.3% (461/528) of non-responders and 69.8% (44/63) of responders at 1 month remained smoking and abstinence at 6 months, respectively [6]. These results supported the need for additional intervention for participants non-responding at the early stage thus to improve the long-term abstinence. For participants already responding to the initial intervention, the remaining initial treatment would be enough.

There are some potential limitations. Due to the nature of adaptive trials with multiple interventions, our study provides limited insight into the mechanisms and effects of each intervention component. Constrained by funding resources, we are not able to assess the long-term effects (e.g. 12 months post-treatment initiation). The quitting outcome at 3 and 6 months enables comparison with most current mHealth smoking cessation trials [1].

## Trial status

This is protocol version 1. Data collection of post-trial qualitative interviews is still in progress.

## Data Availability

Not applicable.

## Abbreviations

AWARD: Ask, Warn, Advice, Refer and Do-it-again
ACE: Adaptive designs CONSORT Extension
BCTs: Behavioural change techniques
CONSORT: Consolidated Standards of Reporting Trials
COSH: Hong Kong Council on Smoking and Health
HSI: Heaviness of Smoking Index
IRB: Institutional Review Board
ITT: Intention-to-treat
mHealth: Mobile health
MI: Motivational interviewing
NRT-S: Nicotine replacement therapy sampling
OCI: Optional combined interventions
PPA: Point prevalence abstinence
ppm: Part per million
PIM: Personalised instant messaging
QTW: Quit to Win
RIM: Regular instant messaging
SMART: Sequential multiple-assignment randomised trial
TTM: Transtheoretical behaviour change model
